## Abstract

**Background:**

The use of adjunctive antibiotics directed against exotoxin production in *Staphylococcus aureus* bacteremia (SAB) is widespread, and it is recommended in many guidelines, but this is based on limited evidence. Existing guidelines are based on the theoretical premise of toxin suppression, as many strains of *S. aureus* produce toxins such as leukocidins (eg, Panton-Valentine leukocidin, toxic shock syndrome toxin 1, exfoliative toxins, and various enterotoxins). Many clinicians therefore believe that limiting exotoxin production release by *S. aureus* could reduce its virulence and improve clinical outcomes. Clindamycin, a protein synthesis inhibitor antibiotic, is commonly used for this purpose. We report the domain-specific protocol, embedded in a large adaptive, platform trial, seeking to definitively answer this question.

**Methods and Analysis:**

The *Staphylococcus aureus* Network Adaptive Platform (SNAP) trial is a pragmatic, randomized, multicenter adaptive platform trial that aims to compare different SAB therapies, simultaneously, for 90-day mortality rates. The adjunctive treatment domain aims to test the effectiveness of adjunctive antibiotics, initially comparing clindamycin to no adjunctive antibiotic, but future adaptations may include other agents. Individuals will be randomized to receive either 5 days of adjunctive clindamycin (or lincomycin) or no adjunctive antibiotic therapy alongside standard-of-care antibiotics. Most participants with SAB (within 72 hours of index blood culture and with no contraindications) will be eligible to participate in this domain. Prespecified analyses are defined in the statistical appendix to the core protocol, and domain-specific secondary analyses will be adjusted for resistance to clindamycin, disease phenotype (complicated or uncomplicated SAB) and Panton-Valentine leukocidin–positive isolate.

*Staphylococcus aureus* bacteremia (SAB) is a common cause of sepsis and invasive infections across the life-course, from neonates to the elderly [1]. It is one of the leading causes of hospital- and community-acquired bloodstream infection, with a mortality rate of up to 30% by day 90 following onset in adults [1]. Multiple virulence factors, enzymes, and exotoxins of *S. aureus* contribute to its pathogenicity [2] including hemolysins, nucleases, proteases, lipases, hyaluronidase, and collagenase [3, 4]. Many strains may also produce leukocidins (eg, Panton-Valentine leukocidin [PVL]), toxic shock syndrome toxin 1, exfoliative toxins, and various enterotoxins [2–4]. Limiting the expression and release of these factors and exotoxins by *S. aureus* could theoretically reduce its virulence, improve clinical outcomes, and ultimately reduce the mortality associated with SAB [5, 6].

Lincosamides, such as clindamycin and lincomycin, function by inhibiting ribosomal protein synthesis, leading to a reduction in the production of multiple exotoxins [6]. Other protein synthesis inhibitor antibiotics that have the potential to inhibit protein production in *S. aureus* include macrolides, linezolid, aminoglycosides, and tetracyclines [7]. Currently, clindamycin is the most frequently used due to its low cost, consistent protein synthesis inhibitor activity [6] and other theoretical advantages include the lack of inoculum effect [8], activity during stationary phase [8], and the repression of penicillin-induced exotoxin production [9, 10].

Human studies involving clindamycin for exotoxin inhibition have shown mixed results but are limited by low-quality evidence arising from case reports, case series, or small clinical trials (Table 1). Several small case reports of patients with *S. aureus* necrotizing pneumonia who received clindamycin or linezolid reported a decrease in PVL in expectorated sputum [11, 12]. In addition, a review of 92 cases of *S. aureus* necrotizing pneumonia (80% of isolates were methicillin-resistant *S. aureus* [MRSA]) found that antibiotic therapy that included an antitoxin agent (clindamycin or linezolid) was associated with lower mortality rates (*P* = .007) [13]. A retrospective study of 269 patients with complex bacterial skin infections (predominantly MRSA) reported a similar length of stay in the adjunctive clindamycin group compared with the monotherapy group (3.7 ± 1.4 days vs 4.0 ± 2.0 days; 95% confidence interval, −0.32 [−.74 to.10]; *P* = .14) [15]. Interestingly, a retrospective review of 289 cases of *S. aureus* infections reported no significant difference in 30-day mortality rates among a small subset of patients receiving adjunctive lincosomide/linezolid therapy in PVL-positive compared with PVL-negative *S. aureus* infections (2.7% vs 5.3%, respectively; *P* = .53) [14].

**Table 1. ciae289-T1:** Human Studies Reporting Adjunctive Clindamycin as an Antitoxin Antibiotic for *Staphylococcus aureus* Infection

Authors (Year of Publication)	Study Design	Sample Size, No. of Patients (Age Category)	Type of *Staphylococcus aureus* Infection	Summary of Study and Primary End-Point Results^a^
Rouzic et al (2010) [11]	Case report	3 (2 Adults; 1 neonate)	*S. aureus* necrotizing pneumonia (2 MSSA and 1 MRSA case)	All 3 patients with severe necrotizing pneumonia survived. Treatment included various antibiotics (clindamycin, linezolid, and rifampicin); 2 patients also received IVIG. One patient each underwent pleural decortication and pleural fluid drainage, and 1 had decreased PVL in sputum with the start of antitoxin therapy.
Pasquier et al (2010) [12]	Case report	2 (Adults)	*S. aureus* pneumonia (MSSA)	Both patients with o severe *S. aureus* pneumonia received clindamycin or linezolid and IVIG, and both survived. PVL detection in expectorated sputum was decreased, but the report did not provide conclusive proof that the improvement and PVL decrease was due to antitoxin therapy.
Li et al (2011) [13]	Case series	93 (Adolescents and adults)	*S. aureus* necrotizing pneumonia (MRSA [80% of isolates] and MSSA)	Retrospective review of 93 cases of *S. aureus* necrotizing pneumonia found that antibiotic therapy including an antitoxin (clindamycin or linezolid) was associated with a lower mortality rate (*P* = .007).
Boan et al (2015) [14]	Case series	289 (Adults)	Skin and soft-tissue *S. aureus* isolates for PVL testing (MSSA and MRSA)	Retrospective review of 141 PVL-positive patients and 148 matched controls (with PVL-negative MSSA or MRSA isolates) reported no significant difference in 30-d mortality rate with adjunctive lincosamide/linezolid therapy in PVL-positive vs with PVL-negative *S. aureus* infections (2.7% vs 5.3%; *P* = .53).
Wargo et al (2015) [15]	Retrospective cohort study	269 (Adults)	ABSSSIs	Retrospective review of 269 patients with ABSSSIs (MRSA in 70% of positive infection site cultures) reported a decrease in LOS, (primary end point) in the adjunctive clindamycin group vs the monotherapy group (3.7 ± 1.4 d vs 4.0 ± 2.0 d; 95% CI, −0.32 [−.74 to .10]; *P* = .14). In patients presenting with an abscess, a significant decrease in LOS was reported for the clindamycin group (3.6 ± 1.5 vs 4.4 ± 2.3 d; 95% CI, −0.82 [−1.49 to −.15]; *P* = .02).
Campbell et al (2022) [16]	RCT	34 (Adults and children)	Severe *S. aureus* infections	Pilot RCT of 34 participants (11 children) reported the primary end point (no. of days alive and free of SIRS) was similar in standard vs adjunctive clindamycin therapy groups. For the secondary outcome, all-cause mortality rate at 90 d, there were no deaths (0/17 [0%]) in the clindamycin vs 4 (4/17 [24%]) in the standard therapy group.

Abbreviations: ABSSSIs, acute bacterial skin and skin-structure infections; CI, confidence interval; IVIG, intravenous immunoglobulin; LOS, length of stay; MRSA, methicillin-resistant *S. aureus*; MSSA, penicillin-resistant, methicillin-susceptible *S. aureus*; PVL, Panton-Valentine leukocidin; RCT, randomized controlled trial; SIRS, systemic inflammatory response syndrome.

^a^Primary end-point results are provided if available.

An Australian and New Zealand practice and attitudes survey in 2019 revealed that 93% of infectious diseases physicians had equipoise and willingness to randomize patients with SAB to receive adjunctive therapy with clindamycin or not [17]. CASSETTE, a recent open-label, pilot, randomized controlled trial (RCT) in adults and children with severe *S. aureus* infections, evaluated the efficacy of standard therapy alone versus standard therapy plus adjunctive clindamycin [16]. Thirty-four participants (23 adults and 11 children) were randomized to adjunctive clindamycin (10 mg/kg per dose up to 600 mg 4 times daily intravenously for adults and children or 10 mg/kg per dose up to 450 mg 3 times daily orally as an optional step-down for adults and children) for 7 days or no adjunctive therapy [16]. Although no difference was detected in the primary outcome of systemic inflammatory response syndrome–free days by day 14, the 90-day mortality rate was 0% (0 of 17 participants) in the adjunctive clindamycin group versus 24% (4 of 17) in the standard therapy group [16]. While the pilot RCT was underpowered to determine the effectiveness of clindamycin, it demonstrated feasibility and provides the rationale to conduct a larger and more robust trial.

The *Staphylococcus aureus* Network Adaptive Platform (SNAP) trial is a multisite adaptive platform trial that will simultaneously answer multiple clinical questions about SAB management [18]. The trial intends to enroll at least 7000 (6000 adults and 1000 children) participants, and it includes key groups who are often excluded from RCTs, such as pregnant participants [19].

Currently there are 3 domains within the SNAP trial, assessing the choice of backbone antibiotics, the role of an early oral switch strategy, and an adjunctive therapy domain, which at this time consists of clindamycin (or lincomycin) compared with no adjunctive therapy. A domain defines a set of mutually exclusive, competing interventions sharing a common clinical mode of action or clinical context of use. SNAP has a core (master) protocol [18] and domain-specific appendices [20] containing specific information relating to the study interventions within each domain. Subgroup-specific appendices contain information related to pediatrics, pregnancy, and people who inject drugs. Each participating site may elect to participate in ≥1 domain. In addition, silos represent the group of participants who are defined by the antibiotic susceptibility of their infecting isolate (eg, methicillin-susceptible *S. aureus* [MSSA] or penicillin-susceptible *S. aureus* [PSSA] and MRSA). The adjunctive domain in the SNAP trial provides an ideal opportunity to test the hypothesis that adjunctive clindamycin is effective in reducing mortality rates in SAB.

## METHODS AND ANALYSIS

### Randomization

At the time of writing, participants are randomized equally to interventions within each domain at platform entry using a web-based module. Participants’ allocation in each domain is revealed at the time that domain-specific eligibility criteria are confirmed.

### Blinding and Unblinding

Once participants are enrolled into the trial platform, those consented to this domain will be randomized to adjunctive therapy (clindamycin or lincomycin) or no adjunctive therapy. Participants, investigators, and site personnel will remain blinded to the allocation until the domain-specific eligibility criteria are satisfied. If the participant is eligible for the domain, the allocation will be revealed, and the investigator and participant will be unblinded. As with all current domains within SNAP, study drugs are open label. On a study-wide basis, investigators, site, and study personnel will remain blinded to aggregate domain outcomes until the SNAP Data Safety and Monitoring Committee recommends halting recruitment to the domain for noninferiority, superiority, or futility or if the maximum platform recruitment target is met.

### Interventions

Table 2 details the interventions and the recommended doses of clindamycin for adult and pediatric participants. Adjunctive clindamycin will be given for 5 days. The recommended clindamycin doses were 600 mg given 3 times daily intravenously in adults and 15 mg/kg per dose with a maximum dose of 600 mg 3 times daily intravenously in children. These were based on French and UK guidelines recommending up to 900 mg per dose [21, 22] (Infectious Diseases Society of America guidelines for MRSA did not recommend adjunctive clindamycin in 2011 [23], with updates currently in progress [24]) and a hollow-fiber model supporting 600 mg as an appropriate dose to inhibit exotoxin production [25, 26]. Clindamycin is the preferred agent, but if unavailable it can be replaced by lincomycin.

**Table 2. ciae289-T2:** Dosing Table for *Staphylococcus aureus* Network Adaptive Platform (SNAP) Adjunctive Domain (Clindamycin) Intervention

Adjunctive Treatment	Dose	Substitutions	Renal Impairment	Oral Alternative
None	…	Nil	…	…
Clindamycin	600 mg (10 mg/kg/dose in children), given intravenously every 8 h for 5 d^a^	Intravenous lincomycin (600 mg every 8 h)	No dosage adjustment	450 mg (10 mg/kg/dose in children), given orally every 8 h

^a^On platform days 1–5.

Administering clindamycin orally is allowed for sites and investigators who prefer oral dosing for reasons of cost, convenience, or antimicrobial stewardship. The oral dose is capped at 450 mg given 3 times daily (Table 2), as this is the maximum licensed dose in most regions and higher doses tend to have poor gastrointestinal tolerability [27]. Study investigators viewed a 5-day course as the shortest duration likely to have clinical impact while balanced against the possibility of adverse effects, particularly *Clostridioides difficile*–associated diarrhea. An initial short-course treatment strategy was also believed to balance the likelihood that any effect of adjunctive clindamycin will be achieved early in the SAB course, while potential gastrointestinal side effects were presumed to be less likely with fewer days of treatment.

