### Statistical Analysis

The primary objective for this domain is to determine whether adjunctive clindamycin is superior to no adjunctive treatment. The SNAP primary end point (90-day mortality rate) is binary and modeled using a Bernoulli distribution with a logistic link function, where the general linear function includes parameters for the effect of each intervention in each domain, silo, and subgroup, interdomain interactions between interventions, ineligibility for a domain, prognostic baseline factors, country nested in region, and (calendar) time epoch. Bayesian methods are used, with weakly informative priors, and permit complete information sharing (borrowing) between silos (MSSA/PSSA/MRSA) for the adjunctive therapy domain (further details available in the published statistical appendix) [28].

The superiority of any intervention versus the domain reference is defined for the adult subgroup based on the posterior probability of an OR of <1 for the primary end point (where an OR <1.0 indicates a decrease in mortality rate for an intervention compared with the reference). A domain-stopping decision will be recommended for superiority if, at a scheduled analysis, the posterior probability of superiority is >99%. A domain-stopping decision of futility will be declared if, at a scheduled analysis, the posterior probability of an OR <0.83 (ie, 1/1.2) for the primary end point is <1%. If the thresholds for the decision criteria are not met within the domain, at any scheduled analysis, then recruitment into the domain will continue.

Scheduled primary analyses will be performed when every cohort of 500 participants in the platform reaches the day 90 end point to evaluate the domain-specific decision criteria. When maximum platform recruitment is reached or domain-specific criteria are satisfied for superiority or futility, then Bayesian analysis and reporting of secondary core and adjunctive domain end points will occur [18]. In addition, prespecified secondary analyses of the primary end point (Table 7) will be performed for the adjunctive therapy domain. Continuous, time to event, and ordinal secondary end points will be modeled using appropriate statistical distributions, link functions, and the same general linear function as for the primary end point, is documented in the published statistical appendix [28].

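### The paediatric intravenous clindamycin dose is given as 15 mg/kg in the Interventions text and 10 mg/kg in Table 2

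*Protocol article*

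**What the plan says.** All of the relevant dosing text is in the Interventions section of the Protocol article.

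- The section points the reader to the table for dosing: "Table 2 details the interventions and the recommended doses of clindamycin for adult and pediatric participants".
- The running text then sets the adult intravenous dose at 600 mg three times daily and the paediatric dose at "15 mg/kg per dose with a maximum dose of 600 mg 3 times daily intravenously in children".
- The clindamycin row of Table 2 reads "600 mg (10 mg/kg/dose in children), given intravenously every 8 h for 5 d". Its only footnote concerns the platform days of administration.
- Table 2 has a separate column for the oral alternative: "450 mg (10 mg/kg/dose in children), given orally every 8 h".

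Three statements elsewhere bear on the point.

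- The introductory text describes the cited pilot randomised trial as using "10 mg/kg per dose up to 600 mg 4 times daily intravenously for adults and children".
- It also says that further documents exist: "Subgroup-specific appendices contain information related to pediatrics, pregnancy, and people who inject drugs". It mentions domain-specific appendices on the study interventions as well.
- The Statistical Analysis section says: "The superiority of any intervention versus the domain reference is defined for the adult subgroup".

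**The concern.** The dose is part of the definition of the intervention. The article prints it twice for children, with different values for the same regimen, so a reader cannot tell which dose is being tested. The trial is recruiting, and the platform plans for "at least 7000 (6000 adults and 1000 children) participants".

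The gap matters for interpretation. The article itself weighs gastrointestinal tolerability when it caps the oral dose, and it makes diarrhoea and *C. difficile* diarrhoea secondary end points. A 50% uncertainty in dose affects how paediatric results on these end points, and on mortality, can be read. It also affects whether anyone can reproduce or apply the regimen.

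**Working it through.** **Do the two statements describe the same regimen?**

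| Feature | Interventions text | Table 2 |
|---|---|---|
| Drug and population | Clindamycin, children | Clindamycin, children |
| Route | Intravenous | Intravenous |
| Frequency | 3 times daily | Every 8 h (= 3 times daily) |
| Duration | 5 days | 5 days |
| Adult dose | 600 mg | 600 mg |
| Paediatric dose | **15 mg/kg** | **10 mg/kg** |
| Stated paediatric maximum | 600 mg | None stated separately |

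Only the mg/kg figure conflicts. Four harmless readings were considered, and none works.

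- *The table entry is really the oral dose.* The oral dose has its own column, and the disputed entry names the intravenous route.
- *15 mg/kg is a ceiling.* The text presents it as the recommended dose and gives 600 mg as the maximum.
- *The text reports a guideline's dose.* It calls the doses based on guidelines, and the adult dose in the same sentence is the trial's own Table 2 dose.
- *It is an alternative that was considered.* The Discussion lists those (900 mg, 3 days, 7 days), and a different paediatric mg/kg dose is not among them.

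**Size of the discrepancy.** With *w* the weight in kg, and 600 mg taken as the cap in both places:

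- text dose = min(15*w*, 600) mg, which reaches the cap at 600/15 = 40 kg
- table dose = min(10*w*, 600) mg, which reaches the cap at 600/10 = 60 kg

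| Weight | Text (mg/dose) | Table 2 (mg/dose) | Ratio |
|---|---|---|---|
| 10 kg | 150 | 100 | 1.50 |
| 20 kg | 300 | 200 | 1.50 |
| 40 kg | 600 | 400 | 1.50 |
| 45 kg | 600 | 450 | 1.33 |
| 50 kg | 600 | 500 | 1.20 |
| 55 kg | 600 | 550 | 1.09 |
| 60 kg | 600 | 600 | 1.00 |

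At 20 kg the daily dose is 3 × 300 = 900 mg against 3 × 200 = 600 mg. Over 5 days that is 4500 mg against 3000 mg.

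The assumed cap in Table 2 matters only above 60 kg, because 10*w* is below 600 mg at every lower weight. With the cap, the two doses are equal from 60 kg. Without it, the table dose would overtake the text dose above 60 kg (at 70 kg, 700 against 600 mg).

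**Does the pilot trial settle which figure is meant?** Below the caps, the daily doses are:

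- text: 3 × 15 = 45 mg/kg/day
- Table 2: 3 × 10 = 30 mg/kg/day
- pilot: 4 × 10 = 40 mg/kg/day

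The text is 45/40 = 1.125 times the pilot's daily dose (12.5% higher) and Table 2 is 30/40 = 0.75 times (25% lower). The pilot's per-dose figure agrees with Table 2, but its frequency and daily total agree with neither. It does not identify the error.

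**The case against.** The strongest counter-argument is that this is a slip in a condensed article with no demonstrated consequence. The appendices carry the operational detail and may give one clear dose. Superiority is defined for adults, whose dose is consistent, and no power figure, error rate or futility rule depends on the paediatric mg/kg figure. The number of children affected is also unknown. Paediatric recruitment needs site approval, the domain's recruitment count is not split by age, and children treated orally have a single consistent figure.

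Much of this stands. No difference in actual site dosing is shown, and none is claimed. Nothing in the article shows that the adult decision is affected. The 50% is the distance between two printed numbers, not an estimate of how exposure varies in the trial. The pilot comparison is context only: the article nowhere says that the paediatric dose should match the pilot, and the domain's schedule differs from it deliberately.

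The objection does not remove the contradiction. This is not detail left to a fuller document. The article states the dose, twice, with different values. An appendix could show which figure is right but could not make both right.

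**Conclusion.** The concern holds: at least one of the two printed paediatric intravenous doses is wrong, and the article does not show which. The text figure is 50% above the table figure up to 40 kg, with the excess falling to zero at 60 kg. Equality beyond 60 kg rests on applying the 600 mg cap to Table 2 as well.

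The point is confined to children given intravenous clindamycin, and it concerns how the article defines their intervention. It should be fixed because it is a drug dose for children in a recruiting trial, but it does not threaten the domain's adult conclusion. Confidence in the contradiction is high. This review takes no position on which figure is correct.

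**What to change.** 1. Check both figures against the approved domain-specific and paediatric appendices.
2. State one paediatric intravenous mg/kg dose, with its maximum per dose, identically in the Interventions text and in Table 2. Table 2 should carry the paediatric maximum explicitly.
3. Only if the appendices contain the same conflict, notify sites of the correct dose and describe paediatric results by dose received.

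Steps 1 and 2 cost a document check and a correction of one figure. Step 3 would add a site notice. No additional patients or procedures are needed.

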### Population

All patients with SAB at participating sites are eligible to participate in the domain, within 72 hours of the collection of the index blood culture.

